### Interim analyses {21b}

Due to the cluster-crossover design, there will be no sufficient data from both treatment conditions to enable the within-center comparisons until near the end of the study. As such, interim analysis for early efficacy or futility would not be informative. Preliminary data will be analyzed only for safety (by tabulating the total percentage of AEs observed) and recruitment rates (by reviewing the total number of patients enrolled and comparing this to predicted rates).

### Methods for additional analyses (e.g., subgroup analyses) {20b}

Subgroup analysis will be conducted for each participating ICU to assess the potential heterogeneity of treatment effects across sites using a generalized linear model stratified by ICU. Additionally, due to standard of care locking differing between CVCs, IVADs, and PICCs (locked with saline) as compared to hemodialysis catheters (locked with citrate), the authors will perform an analysis of the hemodialysis population both together and separately from the rest of the patient population.

During the COVID-19 pandemic, the expansion and shuffling of ICU and HAU patients to different units of the hospital pose a logistical problem in running experimental protocol (as this would involve having to provide education and oversight of nursing staff beyond the ICU/HAUs). As such, patients who are still designated as ICU/HAU care level, but physically located in another unit, will not receive the locking intervention and will be followed by Research Coordinators for their location in the study. Should they be repatriated back to the physical spaces of the ICU/HAU, they will resume receiving the study locking protocol. Because these patients would have experienced an interruption to the experimental protocol, they will also be analyzed in a separate subgroup.

Finally, recent studies have also provided evidence of a higher risk of catheter occlusion and catheter-associated venous thrombosis among COVID-19 patients, due to the hyper-inflammation and hyper-coagulation associated with the virus [35–37]. As such, we will be collecting data about the COVID-19 status of each enrolled patient. This subgroup will also be analyzed separately, to determine if there are any differences among the COVID-19 population.

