### Trial design {8}

The trial is a multi-center, cluster-randomized, double-blinded, crossover trial. Five ICUs/high acuity units (HAUs) across Canada will participate. The ICU/HAUs will be assigned at random to administer either the 4% EDTA locking solution (intervention) or the standard of care saline or citrate (control) during the first four-and-a-half-month period. ICU/HAUs will then cross over and administer the other locking solution during the second 4.5-month period. Patient recruitment will cease at the end of three-and-a-half months during each period to ensure all patients can be followed for 28 days. The study protocol will commence at each site via a staggered start (see Fig. 1).

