### Assignment of interventions: allocation

#### Sequence generation {16a}

Randomization involves only the allocation of the five ICUs to the locking solution that will be used during the first period. The randomization will be performed by a statistician at the Centre for Health Evaluation and Outcome Services (CHEOS).

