## Statistical methods

### Statistical methods for primary and secondary outcomes {20a}

Data will be analyzed following the intent-to-treat principle. The primary outcome will be analyzed using a zero-inflated negative binomial (ZINB) model that accounts for clustering within ICU [33]. The ZINB model takes into account: (1) the large percentage (~ 80% expected) who will not have any event and (2) the large variability in the number of events among participants who experience at least one event (individuals who experience one event are more likely to experience additional events). The (log-)time-at-risk will be entered into the model as an offset term. The average treatment effect will be obtained by regression standardization of the composite incidence rates predicted by the ZINB model [34]. Standard errors will be obtained using bootstrapping.

The model will adjust for the study period (first or second) and may adjust for the following individual-level baseline characteristics: age; sex at birth; BMI; APACHE IV score; length of pre-ICU hospital stay (days); presence of multiple CVADs per patient; any suppression of the immune system, defined as post-organ transplantation, acquired immunodeficiency syndrome [AIDS], neutropenia [< 1000 absolute neutrophils], corticosteroids [> 20 mg/day of prednisone or equivalent for more than 6 months], or currently taking immunosuppressive agents (i.e., Imuran, etc.) at time of enrollment into study; site of CVAD insertion (femoral, jugular, subclavian, right or left side); type of catheter used; any catheter additives, as they may confound the result (such as antibiotic impregnation); having a pre-existing central line upon admission to the ICU; and this line had already received a lock, concurrent systemic antibiotic use unrelated to central line infection, concurrent systemic anti-fungal agent use unrelated to central line infection, concurrent systemic administration of anti-coagulants unrelated to catheter occlusion, type of hemodialysis (if applicable), and previously experienced CLABSI or CVAD occlusion.

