### Methods in analysis to handle protocol non-adherence and any statistical methods to handle missing data {20c}

We do not expect any issues related to protocol non-adherence as detailed education about trial procedures will be given to all the clinical staff involved prior to the study start. No cross-over is expected; only one of the two locking solutions will be available at each site during each period.

We do not expect to have a significant number of missing data points as we are not including any measures that need to be collected outside of the standard of care. Multiple imputation will be used to fill in missing data on covariates, if needed. Should any outliers arise, we will conduct a sensitivity analysis to assess their impact on the conclusions.

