## Discussion

With regard to the decision to exclude readmissions, results from the 1-month pilot study at the lead site indicate re-admission is rare (< 2% of admissions), so their exclusion has a negligible impact on the study results.

Anecdotal evidence gathered from 4% tetrasodium EDTA manufacturers (SterileCare Inc.) acknowledges that aspiration of the standard of care locks prior to flushing procedures or medication administration is not usually done in everyday practice; the locking fluid from the CVAD is flushed into the patient circulation. This poses no harm to the patient. As 4% tetrasodium EDTA solution is only approved by Health Canada as a locking solution, and not as a flush, these procedures will have to change during study operation and nurses will have to aspirate all locked CVADs every 12 h (or 72 h for hemodialysis catheters). This will be included in the education of ICU staff prior to the procedure start.

Finally, multiple crossover events were considered while designing the trial protocol [36]. The benefit of multiple crossovers includes the potential of higher statistical power. This was cautiously weighed against an increase in the experimental timeline due to the increased number of follow-up periods with multiple crossover events. Due to considerations of time and funding, the authors have opted to perform a study with only one crossover event.

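### The ICU-stratified model for site heterogeneity cannot adjust for study period, so each ICU's estimate is a treatment effect only if that ICU has no period effect

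*Protocol article*

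**What the plan says.** The section on additional analyses {20b} plans a subgroup analysis for each participating ICU, to assess "heterogeneity of treatment effects across sites using a generalized linear model stratified by ICU". It states no assumption about period and adds no caveat.

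The design leaves two cells per ICU:
- Trial design {8}: "ICU/HAUs will then cross over and administer the other locking solution during the second 4.5-month period".
- Discussion: "the authors have opted to perform a study with only one crossover event".
- Non-adherence and missing data {20c}: "only one of the two locking solutions will be available at each site during each period".
- Sequence generation {16a}: "Randomization involves only the allocation of the five ICUs to the locking solution that will be used during the first period".

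For the primary outcome {20a} the plan does treat period as something to remove: "The model will adjust for the study period (first or second", followed by a list of optional individual-level covariates. Trial design {8} also says: "The study protocol will commence at each site via a staggered start".

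**The concern.** In a single-crossover cluster design, the treatment effect is separated from the period effect by combining ICUs that took the two locks in opposite orders. A model fitted inside one ICU discards that information. Its treatment coefficient carries the whole change between that ICU's two periods.

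The protocol itself gives reasons why such a change could occur. It describes pandemic-related movement of patients and a higher occlusion risk with COVID-19 {20b}. It also describes an aspiration procedure that will be new to nurses (Discussion), and recruitment that began in March 2022 and is expected to end around August 2023 (Trial status). The analysis could show sites disagreeing when they do not, or agreeing when they do not. This is a stated method at odds with its stated purpose, not a detail left to the analysis plan.

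**Working it through.** **Inputs from the protocol.** 5 ICUs, 2 periods, one lock per ICU-period; risks of 20% and 14%; 1690 patients in total, so 1690/10 = 169 per ICU-period (the recruitment section forecasts 175).

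**The plan's own figure.** The by-ICU analysis has no sample size of its own. The overall 1690 reproduces. With 845 per arm and a cluster-period SD of 0.001, SE = √[(0.20·0.80 + 0.14·0.86)/845 + 2·0.001²/5] = 0.0182 and 0.06/0.0182 = 3.29. With 10 − 2 − 1 = 7 degrees of freedom and an assumed two-sided 5% level, power is about 80%. The point below does not depend on this.

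**Identification.**
- One ICU with intercept, period and treatment: 3 parameters, 2 cells, rank 2. In a control-first ICU treatment equals the period indicator; in an EDTA-first ICU it equals one minus it. Patient covariates do not break this, because the lock is constant within an ICU-period.
- All ICUs with 5 ICU terms, a common period and 5 ICU-specific treatment effects: 11 parameters, rank 10. No single ICU's effect is estimable. Differences are estimable only between ICUs with the same sequence.
- All ICUs with 5 ICU terms, period and one treatment effect: 7 parameters, rank 7. This structure is identified.

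**Size of the distortion.** The period ratios are assumptions; the protocol gives none. With true rate ratio θ in every ICU and common period ratio π (second to first):
- EDTA-first ICU shows θ/π.
- Control-first ICU shows θ·π.
- Spurious gap = π².

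| π | EDTA-first | Control-first | Gap |
|---|---|---|---|
| 1.1 | 0.70/1.1 = 0.64 | 0.70·1.1 = 0.77 | 1.21 |
| 1.2 | 0.70/1.2 = 0.58 | 0.70·1.2 = 0.84 | 1.44 |
| 1.3 | 0.70/1.3 = 0.54 | 0.70·1.3 = 0.91 | 1.69 |

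The reverse also holds. At π = 1.2, true ratios of 0.84 in EDTA-first and 0.583 in control-first ICUs would both appear as 0.70, which hides a real 1.44-fold difference.

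If period effects differ by site, two control-first ICUs with assumed period ratios of 0.8 and 1.2 would show 0.70·0.8 = 0.56 and 0.70·1.2 = 0.84 despite the same true effect.

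**How often a test would be misled.** The plan names no heterogeneity test, so a Cochran Q test on the five by-ICU log odds ratios stands in. The simulation used 20,000 runs, 175 patients per cell, an assumed 2:3 sequence split and a true odds ratio of 0.65 in every ICU. False-positive rates at the 5% level were 4% with no period effect, 7% at a period odds ratio of 0.9, 20% at 0.8 and 48% at 0.7.

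**Precision.** Treating the outcome as a binary risk, the SE of one ICU's log risk ratio is √[((1/0.20 − 1) + (1/0.14 − 1))/169] = √(10.143/169) = 0.245. The 95% limits are a factor of exp(1.96·0.245) = 1.62 either way; around 0.70 that is 0.43 to 1.13. Power to detect 20% against 14% within one ICU is about 31% with 169 per period and 32% with 175.

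**The case against.** The strongest reply is that the aliasing does not destroy all information. A by-ICU contrast is a valid treatment estimate if that ICU has no material period effect. If the period effect is common to all ICUs, those sharing a sequence carry the same bias and can be compared with one another, which keeps 3 of the 4 heterogeneity degrees of freedom under a 2:3 split. A smooth calendar trend could be modelled within an ICU under a stated assumption, and COVID-19 status is recorded per patient, so part of the pandemic case mix is observed. All of this stands. A reader might infer that site heterogeneity cannot be estimated at all; the design does not support that. But {20b} states none of these assumptions, and a model stratified by ICU cannot include the period term.

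A reader might also infer that sites will visibly split by sequence. The staggered start speaks against assuming so: the two periods fall on different dates at different sites, so season or pandemic waves need not act alike everywhere. Learning follows study period more directly. Site-varying calendar effects still bias individual ICU estimates and also undermine the same-sequence comparisons.

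The period ratios are illustrative. The only related planning figure, a cluster-period SD of 0.001, lends them no support; at that value the simulated false-positive rate stays at 4%. It describes assumed random variation, however, and does not exclude a systematic shift. Even at a period odds ratio of 0.8, about 80% of trials would show no significant heterogeneity.

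Finally, this is an additional analysis with no decision rule attached, which limits the consequences.

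**Conclusion.** The concern holds in a limited form. As written, the ICU-stratified model gives each ICU's treatment effect only under an unstated assumption of no period effect in that ICU. The protocol does not make that assumption in its primary analysis, where it adjusts for period. Without it, differences between sites confound treatment heterogeneity with period change.

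The aliasing follows from the design and needs no numerical assumption. The size does: gaps of 1.21 to 1.69 rest on assumed common period ratios of 1.1 to 1.3, and the factor of 1.6 in precision rests on a binary simplification of an outcome that is counted per catheter day and can recur. The primary analysis is not touched, since ICU, period and a single treatment effect are jointly identified.

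**What to change.** Do not use the ICU-stratified models as the test of heterogeneity. Assess it in one pooled model with ICU, study period and a random treatment-by-ICU effect. State that this assumes a period effect common to all ICUs, and that it will be imprecise: ten ICU-period cells less seven mean parameters leave three degrees of freedom for that variance.

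Alongside it, show each ICU's event rates by period and lock descriptively. State there that by-ICU contrasts are conditional on no period effect, and that one crossover cannot separate site-specific treatment effects from site-specific period changes.

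The cost is a little more analysis work and a weaker by-site claim. No change to design, data collection or the primary analysis is needed, and it can be written into the analysis plan that the protocol promises before unblinding.

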### Methods in analysis to handle protocol non-adherence and any statistical methods to handle missing data {20c}

We do not expect any issues related to protocol non-adherence as detailed education about trial procedures will be given to all the clinical staff involved prior to the study start. No cross-over is expected; only one of the two locking solutions will be available at each site during each period.

We do not expect to have a significant number of missing data points as we are not including any measures that need to be collected outside of the standard of care. Multiple imputation will be used to fill in missing data on covariates, if needed. Should any outliers arise, we will conduct a sensitivity analysis to assess their impact on the conclusions.

### Plans to give access to the full protocol, participant-level data, and statistical code {31c}

Participants may request access to de-identified data. Patient-specific data will be available at the completion of data analysis.

### Oversight and monitoring

#### Composition of the coordinating center and trial steering committee {5d}

The daily operations of this project will be managed by site research coordinators. Each center will appoint a research coordinator responsible for enrollment and daily data collection, as well as recording of AEs. Any AEs and enrollment numbers will be communicated to a separate trial steering committee on a bi-weekly basis by each site research coordinator. The trial steering committee will consist of co-investigators and will meet via teleconference on a bi-weekly basis, starting at 4 weeks prior to the study start to discuss trial progress and any necessary protocol amendments. The last meeting will be held 4 weeks after the study end. The trial steering committee will also be responsible for producing the final paper for publication. The data collection database will be according to the internal standard operating procedures.

#### Composition of the data monitoring committee, its role, and reporting structure {21a}

Four percent of EDTA solution has a very low possibility of harm as it is already Health Canada approved, is marketed, and is sold, and patients have minimal systemic exposure as it will be aspirated prior to the lumen being used. As such, investigators feel a standing DMC is not necessary. If at any time, more than 3 serious adverse events are recorded, a DMC will be assembled to review the trial safety.

#### Adverse event reporting and harms {22}

Information about any AEs will be collected with routine data collection. AEs will include (1) local site irritation or redness following accidental administration of the catheter lock into the patient circulation, (2) dysgeusia following accidental administration of the catheter lock into the patient circulation, (3) paresthesia following accidental administration of the catheter lock into the patient circulation, (4) pain upon accidental administration of the catheter lock into the patient circulation, (5) “head rush” following administration, (6) blood rush to face and lips following administration, (7) hypocalcemia due accidental administration of the catheter lock into the patient circulation, and (8) any other adverse reaction observed during accidental administration of the catheter lock into the patient circulation.

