#### Intervention description {11a}

Upon admission to the ICU/HAU, any patient with a CVAD requiring locking who meets the criteria will be enrolled in the study. The patient will receive either a standard of care lock or a 4% tetrasodium EDTA locking solution depending on the randomization status of their treating hospital. Syringes containing either 4% tetrasodium EDTA solution or standard of care locking fluid to be used during locking procedures (called “locking kits”) will be prepared ahead of time by the research pharmacy according to the randomization status of the unit. They will be clearly labeled for use as a locking solution only and placed at the patient’s bedside. Syringes will be prepared with an additional label to remind nurses not to use them in pregnant patients or in those who decline any blood products. In addition to the bedside assessment, research coordinators will review each patient that has received a locking solution every day to gather data and to ensure compliance with the study protocols. Nurses will use the prepared syringes to lock and maintain each CVAD according to the standard of care. Syringe supply at each patient’s bedside will be replenished as needed by the research pharmacy and research coordinators. Enrollment can occur 24 h per day, 7 days per week as nurses can obtain locking syringes specific to the randomization status of the unit at all times.

Medication, maintenance fluids, pressors, or anesthesia will be administered through the CVAD according to the standard of care. Once a lumen of the catheter is no longer being utilized for continuous infusions, leftover medication will be aspirated and flushed with 20 mL of 0.9% sodium chloride using a turbulent flush method as per the standard of care. For patients randomized into the experimental group, the catheter will then be locked with the appropriate volume of 4% tetrasodium EDTA, as specified by catheter manufacturer instructions. These procedures will remain exactly the same for patients randomized into the control group with the exception of using saline or citrate as a locking fluid. Experimental and control solutions are indistinguishable by visual inspection.

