All further catheter procedures and maintenance will proceed according to the standard of care. For all locked catheters, the frequency of flushing will occur every 12 h (or 72 h for dialysis catheters). During this procedure, catheters locked with the standard of care lock will be aspirated, flushed with 10 mL of 0.9% sodium chloride using turbulent flow, and re-filled with the appropriate volume of the standard of care lock. Procedures will stay exactly the same for patients in hospitals randomized to administer the 4% tetrasodium EDTA treatment, except for continued locking with 4% tetrasodium EDTA. Neutral displacement cap change procedures will remain unchanged in both groups. This includes a change every 96 h, after a blood draw through a cap, if removed, contaminated, damaged, and as needed.

Regular assessments of the site of insertion, CVAD system, and patency will continue according to the standard of care, regardless of the type of locking solution used. According to the adult CVAD maintenance record used at each hospital, nurses will assess that dressing is secure, dry, and intact and will palpate the site and check the system at the beginning of each shift. The site of insertion and connections will be reassessed every 4 h as is standard protocol. Dressing and tubing changes will also proceed according to the standard of care in both groups.

Should a locked line (locked with either standard of care or 4% tetrasodium EDTA solution) needs to be re-opened for additional medication administration, the line will be assessed for patency, aspirated of locking solution, and flushed with 20 mL of 0.9% sodium chloride before administering further medication. Patency will be assessed by the ability to aspirate for blood return and the ability to flush a CVAD without resistance prior to the administration of medications and solutions. If the line is not patent, the nurse will assess for occlusions and proceed with the standard of care occlusion diagnosis and treatment. As per the standard of care, CVADs will continue to be removed at the earliest opportunity for each patient. Four percent of EDTA has been shown to be safe if it is inadvertently flushed into the patient, thereby ensuring an adequate safety profile for use with these vulnerable patients.

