#### Relevant concomitant care permitted or prohibited during the trial {11d}

Clinical care will continue as per the discretion of the patient’s healthcare team. The intervention is a CVAD locking fluid that remains only in the lumen of the CVAD; it will never actually enter the patient’s circulation. The locking fluid will be aspirated out of the catheter following the end of locking. As such, there is no potential for drug interactions, and we do not foresee any restrictions in enrolling patients based on other types of concomitant care.

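### Six of the eight listed adverse events, including hypocalcemia and the catch-all, are defined around an accidental flush of the lock, so a reaction with no recognised flush fits none of them

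*Protocol article*

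**What the plan says.** Adverse event reporting and harms {22} opens by stating that information on any adverse event will be collected with routine data, then says what adverse events will include, as eight numbered items. Items 1 to 4 (irritation or redness, dysgeusia, paresthesia, pain) are each placed after or upon accidental entry of the lock. Items 5 and 6 (head rush, blood rush to face and lips) refer to administration without calling it accidental. Item 7 is "hypocalcemia due accidental administration of the catheter lock into the patient circulation". Item 8, the catch-all, is "any other adverse reaction observed during accidental administration of the catheter lock into the patient circulation".

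Several other sections bear on this:

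- Table 1, under Participant timeline {13}, schedules adverse events at first lock and during the locking period, with no flush condition.
- Who will be blinded {17a} blinds care providers and outcome assessors to the solution.
- Interim analyses {21b} reviews safety "by tabulating the total percentage of AEs observed".
- Frequency and plans for auditing trial conduct {23} has all adverse events reviewed by the principal investigator and reported to ethics boards within 72 h.
- Intervention description {11a} accepts that entry can happen: "Four percent of EDTA has been shown to be safe if it is inadvertently flushed into the patient".

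**The concern.** A catch-all item normally closes a list by taking in whatever the named items miss. This one repeats the restriction and tightens it: the reaction must be observed during the accidental entry, so a reaction that begins some time after a known flush is literally outside it.

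Hypocalcemia is the only listed event that is a laboratory value. It could be counted without anyone having seen a flush. Its definition nevertheless requires both a flush and a causal link, and the staff judging that link do not know whether the lock was EDTA.

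What is at stake is how the harm table can be read. A low percentage of adverse events could mean few reactions or few recognised flushes. That matters here because Background and rationale {6a} says 4% EDTA has not been studied in intensive care, the consent waiver in {26a} rests partly on the absence of reported adverse outcomes, and {21a} provides no standing data monitoring committee.

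**Working it through.** **1. Count of conditional items.** Items in {22} that name accidental administration: 1, 2, 3, 4, 7 and 8. That is 6/8 = 75%. Items 5 and 6 do not.

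**2. Where an event without a recognised flush would go.** Take a low calcium during locking, with no flush noticed. It fails item 7 (no flush, no attribution) and item 8 (not observed during a flush). Take a reaction of a kind not listed, again with no flush noticed. It fails item 8. What remains is the opening reference to any adverse event, the row in Table 1, and the duty in {5d} and {23} to pass adverse events on. None of these gives a wider definition of an adverse event.

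**3. Could a flush go unrecognised?** The Discussion gives anecdotal evidence, from before the trial, that "aspiration of the standard of care locks prior to flushing procedures or medication administration is not usually done in everyday practice". The trial requires aspiration in both arms, trains staff, and has coordinators review each locked patient daily "to gather data and to ensure compliance with the study protocols". Flushes should therefore become less common. Nothing in the document shows that they stop or that each one is noticed. This step is an inference from the wording, not something the protocol states.

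**4. What a clean table would exclude (illustration).** The protocol gives no figure to reproduce. Sample size {14} requires 1690 patients. Assume half receive EDTA, n = 1690/2 = 845, treated as independent. With zero recorded events of one type, the one-sided 95% upper bound on per-patient risk is

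U = 1 − 0.05^(1/n) = 1 − 0.05^(1/845) = 0.354%.

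With the 1750 patients expected under Recruitment {15}, n = 875 and U = 0.342%.

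If only a share q of events is recorded, the table bounds q × risk, so the bound on the risk itself is U/q. The values of q are assumed:

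| q | Bound on risk |
|---|---|
| 1 | 0.35% |
| 0.9 | 0.39% |
| 0.5 | 0.71% |
| 0.25 | 1.42% |

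The document gives no flush rate, recognition rate or calcium effect, so it cannot say which row applies.

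**5. Load if every low calcium entered the 72-h stream.** If 5% to 25% of patients (assumed) had a low calcium while locked: 0.05 × 1690 = 84.5 and 0.25 × 1690 = 422.5, about 85 to 423 reports. This is a reason to route calcium through the final safety tabulation instead.

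**The case against.** The strongest reply is that the list need not be the boundary of collection. The section opens with any adverse event, the verb is inclusive, Table 1 has no flush condition, and coordinators report adverse events bi-weekly. The article is also a condensation: the full protocol and case report forms may hold a broader definition and an attribution field. Finally, tying events to exposure is defensible for an approved product with minimal systemic exposure.

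Part of this stands. A reader might infer that all other events will be discarded; the opening sentence and Table 1 do not support that. What does not fall away is that the article states a definition, and its catch-all works against the broader reading. Coordinators at five sites could apply it differently.

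Other stronger readings also fail:

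- A reader might infer that blinding causes missed flushes. Blinding hides which solution is in the lumen, not whether the lumen was aspirated; an unblinded nurse would also have to notice the flush. Blinding bears only on the causal judgement in item 7.
- A reader might infer from the Discussion that flushes will be frequent. That remark is anecdotal, concerns standard of care locks, and comes with its remedy of training and mandatory aspiration. The adherence criterion in {15}, more than 85% of patients, covers the whole protocol and is not a flush rate.
- A reader might add the statement in {11d} that "it will never actually enter the patient’s circulation". It is stronger than {11a} allows, but it describes intended use, and editing it would change no result.
- The trigger in {21a} of more than three serious adverse events is not tied to this list, so nothing shows that it is weakened.

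**Conclusion.** The point holds as a flaw in how harms are defined. Six of eight listed events depend on an accidental flush, and the catch-all carries the same condition, so a literal reader has no listed place for a low calcium or other reaction without a recognised flush. The count is certain. That events will be missed depends on staff following the list literally and on some flushes passing unnoticed; both are plausible and neither is established. The under-count cannot be sized, and the bounds of 0.35% to 1.42% rest on assumed recording shares and independent patients. The primary comparison is untouched. This is a cheap improvement to the safety record, worth making but not a threat to the main result.

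**What to change.** - **Item 7.** Count hypocalcemia as any value below the laboratory limit on clinically ordered bloods from first lock to the end of the locking period, whether or not a flush was seen. Extract it from charts for both periods at every site, so that the arms stay comparable although recruitment began in March 2022. This assumes calcium is measured in usual intensive care.
- **Item 8.** Reword to: *any other adverse reaction observed during the locking period, whether or not the lock is known to have entered the circulation*.
- **Attribution.** Record known or suspected lock entry (yes, no, unknown) as a separate field. Tabulate events by arm and by that field at the final analysis. Leave the pooled tabulation in {21b} unchanged.
- **Reporting.** Present the chart-extracted calcium values as a safety outcome in the final tabulation, so that the 72-h ethics rule in {23} stays as it is.

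Items 1 to 6 can stay. Rewriting every symptom definition partway through a single crossover could make recording differ between periods, and so between arms within a site. Item 8 carries a smaller version of that risk: reactions not recorded before the change cannot be recovered from charts as calcium can, so note the date of change at each site.

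The cost is more background events from critical illness in both arms, some extra chart extraction, and an amendment approved by the ethics boards as {25} requires. Arms, blinding, sample size and the primary analysis do not change.
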